### Objectives

The primary objective of the study is to determine whether the incidence of PH is lower in CDH patients treated with intravenous sildenafil than in patients treated with iNO, with the primary outcome defined as the absence of PH on echocardiography on day 14 without pulmonary vasodilator therapy and without treatment failure and/or death within the first 28 days after birth. PH is defined as systolic pulmonary arterial pressure >2/3 systolic systemic pressure and/or right ventricular (RV) dilatation/septal displacement and RV dysfunction +/−left ventricular dysfunction.

The secondary outcomes are:

Change in OI after 12 and 24 hours of therapy.Overall mortality.The incidence of treatment failure which is defined as:inability to maintain preductal saturations above 85% (±7 kPa or 52 mm Hg) or postductal saturations above 70% (±5.3 kPa or 40 mm Hg).and/or increase in CO_2_ >70 mm Hg (9.3 kPa) despite optimisation of ventilator management.and/or inadequate oxygen delivery with metabolic acidosis defined as lactate ≥5 mmol/L and pH <7.15 and/or hypotension resistant to fluid therapy and adequate inotropic support resulting in a urine output <0.5 mL/kg/hour.and/or lactate ≥5 mmol/L and pH <7.15.and/or OI consistently ≥40.Time on intervention drug, defined as intervention drug free days after initiation of the intervention, calculated on day 14.Need for ECMO.Ventilator free days on day 28.The use of drugs for PH treatment during the hospital admission.The use of pulmonary and/or cardiac medication at discharge and its total duration of administration.Short-term and long-term PH on echocardiography at 24 hours, 28 days/discharge and 6 and 12 months.The incidence of chronic lung disease.The development of neurological abnormalities evaluated with ultrasound of the brain before the start of the trial, after surgery and before discharge.The external validation of the sildenafil pharmacokinetic - pharmacodynamic (PKPD) model for the pharmacokinetics and the pharmacodynamic effects of sildenafil.

Safety outcomes include adverse events due to the study drugs and the vasoactive-inotropic support (VIS) score.

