#### ​Randomisation, intervention and blinding

Participants will be randomised using ALEA, which is an online, central randomisation service (https://www.aleaclinical.eu). Allocation concealment will be ensured, as the service will not release the randomisation code until the patient has been recruited into the trial, which takes place after all baseline characteristics have been added. ALEA randomises the patient with a computer-generated randomisation list, made by the independent statistician of the Data Safety and Monitoring Board. Blocked randomisation, with variable block sizes and stratification by centre, is used to achieve equal distribution of the two interventions among the participants.

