### Sample size calculation

The sample size calculation is based on a power analysis for the primary outcome, using previously published data on PH. Lusk *et al* showed that PH, defined as >2/3 systemic blood pressure measured on echocardiography, in CDH patients on day 14 has a positive predictive value of 0.8 for death, death or ventilation, and death or ventilator support. PH on day 14 is observed in 64% of CDH patients.^24^

Even though the definition of the primary outcome is not the same, we assume a similar outcome percentage of 64% for failing the primary outcome in our trial, the absence of PH on day 14 without pulmonary vasodilator therapy and/or absence of death within the first 28 days of life, in the iNO group. Our aim is to promote practice change; therefore, we aim for a clinically significant difference. For a 25% relative reduction to 48%, a sample size of 300 patients (150 patients per group) is needed to obtain a power of 80%. This will match a number needed to treat of 6.25. Taking missing data and the effects of correction for covariates into account, we adjust this sample size to 330 patients. In the collaborating centres 550 patients will be born in 3 years. Based on our earlier trial (CMV Versus HFO in Congenital Diaphragmatic Hernia; VICI trial) we expect to have an inclusion rate of 60%. Therefore, the inclusion of 330 patients should be reached in 3 years.

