### Data analysis

The patients will be analysed according to the group they are randomised to (intention-to-treat analysis). A p-value (two-sided) <0.05 is considered significant in all analyses. The primary endpoint will be analysed using multiple logistic regression with randomisation arm, centre, observed/expected head-lung ratio, position of the liver, side of the defect, defect size and ventilation modality as independent variables.^25^ If necessary, multiple imputation using the fully conditional specification method will be used to account for missing data in the independent variables. We will perform a sensitivity analyses with adjustment for the use of prostin and milrinone, to account for the effects of these vasodilators on PH.

The following analyses will be performed for the secondary outcomes. The distribution of VIS score in all study participants will be compared between t=0 and t=12 hours after initiation of drug administration using a Wilcoxon signed rank test. The distribution of changes in OI and VIS score from t=0 to t=12 and t=24 hours will be compared between the randomisation groups with a Mann-Whitney test. The overall mortality in the first year of life will be compared between the randomisation groups with Kaplan-Meier curves and the log-rank test. The number of treatment failures, the need for ECMO (in ECMO centres) and the need for medication for PH or chronic lung disease at discharge, and during the first year of life, will be compared between randomisation groups with χ^2^ tests. The number of study drug free days at day 14, the number of ventilation-free days until day 28, the fraction of days with need for medical treatment (excluding the study drug) for PH during the hospital admission and the severity of chronic lung disease using the Bancalari definition will be compared between randomisation groups using Mann-Whitney tests. Deaths will be counted as the worst outcome in these analyses, in accordance with the intention-to-treat principle. The presence of PH at 28 days/discharge, 6 and 12 months according to the echocardiographic parameters will be compared between randomisation groups with a χ^2^ test.

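### The Mann-Whitney tests on change in OI and VIS use baseline only by subtraction and leave out centre: valid under randomisation, but less precise than a baseline-adjusted comparison

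*Protocol article*

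**What the plan says.** The Objectives section lists "Change in OI after 12 and 24 hours of therapy" among the secondary outcomes and names VIS as a safety measure: "Safety outcomes include adverse events due to the study drugs and the vasoactive-inotropic support (VIS) score". Table 1 schedules both scores before therapy, at 12 hours and at 24 hours.

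The Data analysis section fixes the method for both: "The distribution of changes in OI and VIS score from t=0 to t=12 and t=24 hours will be compared between the randomisation groups". The test is the Mann-Whitney test. No baseline covariate and no stratified form is mentioned.

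On allocation, the section on randomisation, intervention and blinding states: "Blocked randomisation, with variable block sizes and stratification by centre, is used". For the primary endpoint, the Data analysis section plans "multiple logistic regression with randomisation arm, centre, observed/expected head-lung ratio, position of the liver, side of the defect, defect size and ventilation modality". Centre and prognostic variables are thus used there but not for OI and VIS.

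**The concern.** A change score is an analysis with the coefficient of baseline set to 1. When the true slope of follow-up on baseline is below 1, subtraction over-corrects. An arm that starts higher by chance then tends to show the larger fall, whatever the treatment does. Estimating the slope removes that component and the variance that goes with it. Leaving out centre, which was balanced by design, discards a further and usually smaller amount of precision.

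The two comparisons matter clinically. The Introduction reports that intravenous sildenafil improved OI but increased the need for inotropic support. Change in OI and change in VIS are the direct randomised checks on that benefit and that harm, and a noisier test is more likely to miss either.

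The article names the test, so this is a stated choice and not a detail left to an analysis plan that is not shown.

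**Working it through.** **The plan's own figure.** The article gives no power or sample size for OI or VIS. Its only calculation is for the primary outcome (64% against 48% failing, two-sided 0.05, 80% power), and it reproduces:

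n per group = [1.96·√(2·0.56·0.44) + 0.8416·√(0.64·0.36 + 0.48·0.52)]² / 0.16² = (1.3759 + 0.5831)² / 0.0256 ≈ 150.

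The 330 used below is the inflated total from the same section.

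**Inputs for this point.**
- From the article: change from t=0 as the analysed variable, Mann-Whitney test, stratification by centre, N = 330.
- Assumed, because the article does not give it: the correlation r between baseline and follow-up, taken as 0.3, 0.5, 0.7 and 0.8.
- Also assumed: equal SDs at baseline and follow-up, so that the slope equals r, and a comparison of means.

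**Variance of the treatment contrast.** In common units:
- change score: 2(1 − r)
- baseline-adjusted: 1 − r²
- ratio: (1 − r²) / [2(1 − r)] = (1 + r)/2

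| r | change score | adjusted | ratio | reduction | change-score N matching 330 adjusted |
|---|---|---|---|---|---|
| 0.3 | 1.40 | 0.91 | 0.65 | 35% | 330/0.65 = 508 |
| 0.5 | 1.00 | 0.75 | 0.75 | 25% | 330/0.75 = 440 |
| 0.7 | 0.60 | 0.51 | 0.85 | 15% | 330/0.85 = 388 |
| 0.8 | 0.40 | 0.36 | 0.90 | 10% | 330/0.90 = 367 |

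**Imbalance left in the comparison.** With 165 per arm, the chance difference in baseline means has SD √(2/165) = 0.11 baseline SD. A share (1 − slope) stays in the change-score contrast with opposite sign: 0.7 × 0.11 = 0.077 SD at slope 0.3, 0.055 at 0.5, 0.033 at 0.7 and 0.022 at 0.8.

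This is not a second harm on top of the variance loss. Since 2(1 − r) = (1 − r²) + (1 − r)², the retained imbalance is exactly the extra variance. At r = 0.5 it is 0.25 of 1.00, which is the 25% in the table.

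**Simulation on a rank scale.** Assumed: 12 centres of 26 infants (312), skewed (lognormal) scores, effect 0.3 SD on the log scale, centre variance 0.1, 1000 runs, Monte Carlo error about ±3 points.
- Power of Mann-Whitney on raw change against rank regression with baseline and centre: 0.43 against 0.69 (r = 0.3), 0.55 against 0.80 (r = 0.5), 0.74 against 0.91 (r = 0.7).
- Much of that gap comes from testing raw differences when the effect is on the log scale. In a separate simulation of the same layout, Mann-Whitney on log change against baseline rank ANCOVA gave 0.53 against 0.72 at r = 0.3, and 0.89 against 0.92 at r = 0.7.
- Adding centre alone gained about 2 to 3 points at centre variance 0.1 and 3 to 6 points at 0.2.
- Type I error of the planned test was 0.035 to 0.052 across all scenarios.

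**The case against.** The strongest reply is that nothing here is an error. Under randomisation a Mann-Whitney test on change is valid, unadjusted rank tests are conventional for skewed secondary outcomes, and the primary endpoint is already adjusted for centre and prognostic variables. All of that stands. The case rests on efficiency alone.

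Some stronger readings are tempting but are not supported:
- **That the plan ignores baseline.** It does not; baseline is subtracted. The complaint is only that the slope is fixed at 1.
- **That OI >20 as an entry criterion makes every baseline high, so that regression to the mean distorts the result.** Under Patients, two of four criteria suffice, so an infant can enter with an OI of 20 or below. VIS is not an entry criterion. Regression to the mean also acts on both arms equally in expectation, so it does not bias the comparison.
- **That the test yields false positives.** The simulated error rates show no inflation, and the test is slightly conservative when centres differ.
- **That baseline adjustment alone is worth 17 to 26 power points.** Those gaps also contain the choice of scale and the effect of centre, in an assumed scenario.

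It is also fair that the variance table needs equal SDs and a comparison of means, and that the article supplies no correlation, SD or effect size for OI or VIS. If the true slope is near 1, the gain is small. What survives is a real loss at low correlation: 0.53 against 0.72 at r = 0.3, even after the scale is put right.

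**Conclusion.** The point holds as a minor one. The planned comparison of OI and VIS changes is valid but avoidably imprecise. Under equal SDs on a mean scale, baseline adjustment would reduce the variance by about 35% at r = 0.3, falling to 10% at r = 0.8. These correlations are assumptions, and the figures indicate the order of magnitude of the loss for a Mann-Whitney test, not its exact efficiency. Centre contributes less. The outcomes concerned are a secondary and a safety measure, so neither the primary analysis nor its conclusion changes. Being listed first among the secondary outcomes gives change in OI no formal priority.

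**What to change.** Replace the Mann-Whitney tests on change in OI and VIS with a model of the 12-hour and 24-hour values on arm, baseline value and centre. Use a log scale or ranks (for example rank ANCOVA), and report an estimate with a confidence interval where the scale allows. Fix the scale before the data are compared by arm.

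Stratifying the other rank tests (van Elteren) and the log-rank test by centre is optional and gains less. A van Elteren test on change in OI or VIS would deal with centre only, not with baseline.

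The cost is a change of analysis wording. Baseline, 12-hour and 24-hour values of both scores are already scheduled in Table 1, so no new data and no further patients are needed.

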Postnatally, infants are treated according to a standardised protocol for patients with CDH, which is implemented in all participating centres. This protocol was developed with the available evidence and consensus between the participating centres and was updated in June 2016.^10 16^ If the patient is diagnosed with PH in the first week of life, the patient will be allocated to one of the two study drugs (figure 1). iNO is provided by a tank connected to a ventilator. Different devices are used in different centres. Some centres use integrated systems, making it impossible to disconnect the iNO tank and replace it with another gas to facilitate a blinded intervention. Therefore, the study is open label. iNO is given with a starting dose of 20 ppm, which is the maximum dose.^18 19^ Sildenafil is given intravenously, using a loading dose of 0.4 mg/kg in 3 hours, followed by continuous infusion of 1.6 mg/kg/day.^20 21^ To wean the study drugs a standard protocol is followed (figure 2). The allocated drugs will be restarted as per protocol if criteria for its use are met again before the age of 14 days. To further standardise care, an inotropic support flow chart is included in the study protocol (figure 3). After day 14 treatment of PH will be at the discretion of the local medical team and the study drug can be changed to, for instance, sildenafil orally. The use of bosentan, milrinone and prostin next to the study treatment is allowed. The use of bosentan as add on therapy is allowed and is considered as PH treatment on day 14. The intervention will be prematurely stopped when the patient meets one or more of the defined failure criteria, described in point three of the secondary outcomes. Further treatment will then be at the discretion of the medical team and will be according to the standardised protocol.^16^ iNO and sildenafil can both be given outside the study protocol. An ECMO procedure may then be started in centres where ECMO is available. Data of all patients are used in the intention-to-treat analysis.

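### First-year mortality and the yes/no secondary outcomes are compared without centre or baseline covariates: valid, but it gives up some precision

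*Protocol article*

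**What the plan says.** Under Randomisation, intervention and blinding, the protocol article states: "Blocked randomisation, with variable block sizes and stratification by centre, is used to achieve equal distribution of the two interventions among the participants".

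Under Data analysis, the primary endpoint is analysed by "multiple logistic regression with randomisation arm, centre, observed/expected head-lung ratio, position of the liver", together with "side of the defect, defect size and ventilation modality as independent variables".

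The same section then names the secondary tests outcome by outcome:
- Death: "The overall mortality in the first year of life will be compared between the randomisation groups with Kaplan-Meier curves and the log-rank test".
- A first group of yes/no outcomes, by χ² tests: "The number of treatment failures, the need for ECMO (in ECMO centres) and the need for medication for PH or chronic lung disease at discharge". The medication comparison also covers the period up to one year.
- Later PH, also by a χ² test: "The presence of PH at 28 days/discharge, 6 and 12 months according to the echocardiographic parameters will be compared between randomisation groups".

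No stratum or covariate is named for any of these. The one sensitivity analysis, adjusting for prostin and milrinone, is described with the primary endpoint.

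**The concern.** Infants are balanced between arms within centre. If centres differ in outcome, a test that ignores centre uses a variance larger than the one the design delivers. The article itself gives a reason why centres may differ: after treatment failure, "An ECMO procedure may then be started in centres where ECMO is available". It does not show that this affects survival.

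Separately, the trial collects prognostic factors at baseline and uses them in the primary model, but not for death or the other binary outcomes.

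Precision on mortality is at stake. The Abstract motivates the trial partly by mortality, and the data safety monitoring board watches it continuously, but the sample size was set for the primary outcome alone. The OI and VIS comparisons by Mann-Whitney test are not part of this point.

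**Working it through.** **1. The plan's own figure.** Inputs from Sample size calculation: 64% v 48% and 80% power. Two-sided 5% is from Data analysis.

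n per group = [1.96·√(2·0.56·0.44) + 0.8416·√(0.64·0.36 + 0.48·0.52)]² / 0.16² = (1.376 + 0.583)² / 0.0256 ≈ 149.9, so 150.

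The stated 150 per group reproduces. The plan's arithmetic is not at issue.

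**2. What that size means for mortality.** The Introduction gives 27% mortality for CDH in general. Assume this for the iNO arm, and assume the same 25% relative reduction as for the primary outcome: 27% v 20.25%, with 165 per arm.

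z = [0.0675·√165 − 1.96·√(2·0.23625·0.76375)] / √(0.27·0.73 + 0.2025·0.7975) = (0.867 − 1.177)/0.599 = −0.52

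Power is therefore about 30%. Mortality has little precision to spare at an effect of that size.

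**3. First simulation.** All inputs except the 330 infants are assumed: 12 centres, about 26% control mortality, treatment log odds ratio −0.85, centre SD 0.5 to 0.8, two baseline predictors with coefficients 0.6 to 0.9, 2,500 runs in each of four settings. The adjusted analysis includes centre and both predictors.

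| Setting | Log-rank power | Adjusted power | Gain (points) |
|---|---|---|---|
| 1 | 78.3% | 82.1% | 3.8 |
| 2 | 75.7% | 81.9% | 6.2 |
| 3 | 77.0% | 81.0% | 4.0 |
| 4 | 71.7% | 78.9% | 7.2 |

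Stratifying by centre alone added about 1 point. Null rejection in settings 1 to 4 was 5.0, 4.6, 3.8 and 4.3% for log-rank, and 4.7, 4.6, 3.6 and 4.3% for χ². The Monte Carlo standard error is √(0.05·0.95/2500) = 0.44 points, so only setting 3 is clearly below 5%.

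**4. Second simulation.** Again 330 infants. Assumed: 15 centres, permuted blocks of 2 and 4 within centre, 27% one-year control mortality, exponential survival, hazard ratio 0.5, 3,000 runs. SDs are on the log-hazard scale. Here the adjusted Cox and logistic models contain the covariate but not centre.

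| Centre SD / covariate SD | Log-rank | Stratified log-rank | Adjusted Cox | χ² | CMH | Adjusted logistic |
|---|---|---|---|---|---|---|
| 0 / 0 | 80.1% | 79.6% | 79.5% | 80.0% | 79.9% | 79.2% |
| 0.5 / 0.5 | 76.9% | 77.8% | 78.5% | 77.0% | 78.1% | 78.2% |
| 0.5 / 1.0 | 67.6% | 69.0% | 77.3% | 67.3% | 68.0% | 74.9% |
| 1.0 / 1.0 | 64.1% | 68.9% | 70.4% | 63.0% | 67.6% | 68.4% |
| 1.0 / 1.5 | 50.9% | 55.3% | 68.7% | 49.4% | 53.8% | 63.2% |

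- Gain from stratifying by centre where effects exist: 0.7 (67.3 to 68.0) to 4.8 points (64.1 to 68.9).
- Gain from baseline adjustment in the two middle cases (0.5/1.0 and 1.0/1.0): 5.4 to 9.7 points. Over all rows with effects it runs from 1.2 (77.0 to 78.2) to 17.8 (50.9 to 68.7).
- With no centre or covariate effect, nothing is gained.

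**5. Type I error in the second simulation.** The Monte Carlo standard error is √(0.05·0.95/3000) = 0.40 points. With centre SD 0 or 0.5, log-rank rejects 4.3% and χ² 4.4 to 4.6%, close to nominal. With both SDs at 1.0, log-rank rejects 2.7% and χ² 3.2%; stratifying brings these to 4.3% and 4.7%. No plain test exceeded 5% in either simulation.

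**6. A smaller effect.** A further run with 12 centres at about 26% v 19% mortality, comparing χ² with logistic adjustment, gave power of 37% to 42% in one setting and 28% to 36% in another. These are gains of 5 and 8 points.

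**The case against.** The article never calls these tests unstratified, and a fuller analysis plan that is not shown could specify stratified versions. That caveat stands. But the section lists covariates where it wants them, so the plain reading is that the secondary tests use none.

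The strongest objection is that nothing here is invalid. A plain log-rank or χ² test after centre-stratified randomisation does not inflate false positives, and the primary analysis is already adjusted. This stands in full, and the point is one of efficiency only.

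The power levels in the two main simulations also rest on roughly halving mortality, an effect found nowhere in the documents: 1 − 0.73^0.5 = 14.6% against 27%. This stands too. The 64 to 82% levels in most settings should not be read as the trial's power for mortality; only the differences carry the argument, and they persist at the smaller effect.

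The ECMO comparison is already confined to ECMO centres, so it does not mix in centres where ECMO is unavailable. That restriction does nothing for mortality or the other binary outcomes.

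Adjustment is not quite free. O/E lung-head ratio is an antenatal measurement, and infants whose CDH was not known before birth can be enrolled, so it will sometimes be missing. Centre strata will also be thin: with 27% and 14.6% mortality, 165 × (0.27 + 0.146) ≈ 69 deaths over 15 assumed centres is fewer than five each.

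**Conclusion.** The point holds as a modest loss of precision on secondary outcomes. Under the assumed effects, stratifying by centre is worth about 1 to 5 points of power and baseline adjustment typically about 4 to 10, with zero gain if centres and covariates do not matter. The number of centres, block sizes, centre variation and covariate strength are not in the documents, so these are ranges under assumptions.

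A reader might infer more than this, in three ways:
- That the mortality comparison is biased or its p-values wrong. The documents and the simulations do not support this: error stays at or below 5%.
- That plain tests after stratified randomisation are always too conservative. Here the shortfall is material, about 3% against 5%, only when centres differ strongly.
- That the trial's main conclusion is affected. It is not, because the primary model already includes centre and the prognostic factors.

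**What to change.** For first-year mortality, specify a log-rank test stratified by centre, plus a Cox model stratified by centre with arm, O/E lung-head ratio, liver position and side of the defect.

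For treatment failure, ECMO (still within ECMO centres), medication and later PH, specify logistic regression with arm, the same covariates and centre, either as a random intercept or with small centres pooled. At the least, use Cochran-Mantel-Haenszel stratified by centre.

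Leave out defect size and ventilation modality unless they are known before randomisation; the article does not say when they are recorded. Extend the multiple imputation planned for the primary model to missing O/E lung-head ratio in these models. State the rule for pooling small centres in advance. Keep the plain tests as supportive.

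The cost is a change of plan wording before the data are seen and a little more analysis work for imputation and sparse centres. No new data are needed and the sample size does not change.

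### Study-drug-free days at day 14 score a surviving treatment failure better than a successful wean; separately, the PH-treatment-days outcome may exclude a different drug in each arm

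*Protocol article*

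**What the plan says.** The Objectives section of the protocol article lists, as a secondary outcome, "Time on intervention drug, defined as intervention drug free days after initiation of the intervention, calculated on day 14". The Data analysis section takes this up as "The number of study drug free days at day 14" and compares it between arms with a Mann-Whitney test. Its scoring rule for the outcomes tested this way is: "Deaths will be counted as the worst outcome in these analyses, in accordance with the intention-to-treat principle". No other event receives a special rank.

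The section on randomisation, intervention and blinding says what happens at failure: "The intervention will be prematurely stopped when the patient meets one or more of the defined failure criteria". Further treatment is then left to the medical team, "iNO and sildenafil can both be given outside the study protocol", and ECMO may be started where it is available.

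A second outcome in Data analysis is "the fraction of days with need for medical treatment (excluding the study drug) for PH during the hospital admission". In Objectives it appears without any exclusion, as "The use of drugs for PH treatment during the hospital admission". After day 14, "the study drug can be changed to, for instance, sildenafil orally".

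**The concern.** A drug-free-days outcome is normally read as more days, better course. That holds only if stopping the drug means the infant no longer needs it. Here the drug also stops because it has failed. The plan already accepts that a bad event which ends exposure must not score well, but it applies this to death alone. An arm with more surviving failures can then look better on this outcome, or a real disadvantage can vanish from it.

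The second outcome raises a different question. Each infant is allocated to one of two study drugs. If the excluded drug is the allocated one, the two arms are measured with different drug lists.

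**Working it through.** **Scope.** The protocol gives no figure for either outcome. Its one sample-size figure does reproduce: for 64% v 48%, n per arm = [1.96·√(2·0.56·0.44) + 0.8416·√(0.64·0.36 + 0.48·0.52)]² / 0.16² = (1.3759 + 0.5831)² / 0.0256 ≈ 150, or 300 in total. It does not depend on these secondary outcomes.

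**Step 1: individual scores.** Drug-free days = 14 − days on study drug, for a start at day 0 (a later start lowers both scores alike).
- Fails on day 2, survives, moved to the other drug or ECMO: 14 − 2 = 12.
- Weaned successfully after 8 days: 14 − 8 = 6.

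**Step 2: arm level, no deaths.** Assumptions, not document figures: failure 50% in the worse arm v 30% in the other; failures stop on days 1–3 (mean 2), others on days 5–11 (mean 8). Mean drug-free days are 0.5·12 + 0.5·6 = 9.0 in the worse arm and 0.3·12 + 0.7·6 = 7.8 in the other.

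**Step 3: adding the death rule.** In each arm let s = surviving failures, w = surviving non-failures and d = deaths. As written, every s outranks every w (at least 14 − 3 = 11 days v at most 14 − 5 = 9), and every w outranks every d. With subscript 1 for the worse arm and 0 for the other, the chance that a worse-arm infant scores higher, counting ties as half, is

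s₁(w₀ + d₀) + w₁d₀ + ½(s₁s₀ + w₁w₀ + d₁d₀).

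Example, mortality 30% in failures and 10% in non-failures: the worse arm has s, w, d = 0.35, 0.45, 0.20 and the other 0.21, 0.63, 0.16. The index is 0.35·0.79 + 0.45·0.16 + ½(0.0735 + 0.2835 + 0.032) = 0.2765 + 0.072 + 0.1945 = 0.543.

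With failures set to zero days, just above death, the order becomes w > s > d and the index is w₁(s₀ + d₀) + s₁d₀ + the same tie term. For the example: 0.45·0.37 + 0.35·0.16 + 0.1945 = 0.417.

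The shares of significant results come from simulation with 165 per arm (330/2) and a two-sided Mann-Whitney test at 0.05.

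| Assumed mortality, failures/non-failures | Deaths, worse v other arm | Index as written | Trials significantly favouring worse arm | Index with failures at zero |
|---|---|---|---|---|
| 0/0 | 0% v 0% | 0.600 | about 87% | 0.400 |
| 30%/10% | 20% v 16% | 0.543 | about 28% | 0.417 |
| 40%/10% | 25% v 19% | 0.524 | about 12% | 0.416 |
| 50%/10% | 30% v 22% | 0.505 | about 4% | 0.415 |
| 60%/10% | 35% v 25% | 0.486 | about 1% | 0.414 |

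An index above 0.5 favours the arm with more failures. At 50%/10% that arm has 20 points more failures and 8 points more deaths, yet the index is 0.505, so the outcome registers almost nothing. With failures at zero, the index points the right way in every row and the simulated share favouring the worse arm is 0%.

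**Step 4: the second outcome.** Suppose that the excluded drug is the allocated one, and take an assumed 40-day stay with the same off-protocol treatment in both arms.

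| Off-protocol days (same in both arms) | Counted, iNO arm | Counted, sildenafil arm |
|---|---|---|
| 10 iNO, 20 sildenafil | 20/40 = 0.50 | 10/40 = 0.25 |
| 20 iNO, 10 sildenafil | 10/40 = 0.25 | 20/40 = 0.50 |

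Identical care gives different scores, and the direction follows whichever drug is used more. Failure is not rewarded here, because rescue with the other drug is counted and raises the fraction.

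**The case against.** Several points on the other side have force.

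- **The death rule already absorbs much of the problem.** It does. The Introduction gives CDH mortality of 27%, and failure as defined (for example OI persistently at 40 or above) plausibly carries excess deaths. The 40%/10% to 60%/10% rows average 22% to 30% mortality over the two arms, and there wrong-direction significance is 12% or less. A reader might take the no-death figure of about 87% as the expected size. The documents do not support that.
- **An excess of failures would be seen elsewhere.** Treatment failure, ECMO, mortality and ventilator-free days are compared separately, and Objectives puts freedom from failure into the primary outcome. This limits the harm but does not make this outcome interpretable.
- **The outcome is labelled as time on drug.** As a pure exposure measure it would need no rank for failure. But it is tested between arms with deaths ranked worst, which makes it a measure of benefit.
- **The term study drug could mean either drug, from any source.** That reading would remove the arm difference in the second outcome and most of the reward in the first, except for infants moved to ECMO on neither drug. The text does not say so, and it describes treatment after failure as outside the protocol.

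Two stronger readings are tempting. One is that both outcomes reward failure; Step 4 shows that the second does not. The other is that the second outcome is biased towards sildenafil because oral sildenafil after day 14 is excluded in that arm only. The allocated drug is intravenous, and something the study drug is changed to is more naturally no longer the study drug. On that reading oral sildenafil counts in both arms. Off-protocol iNO, counted only in the sildenafil arm, pulls the other way.

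**Conclusion.** The point holds for study-drug-free days as a matter of the stated rules: drug stopped at failure, other treatment allowed, only death ranked worst. The direction for a surviving early failure follows from the wording, with study drug read as the allocated drug given under the protocol. The size does not. Under the assumed 50% v 30% failure rates it runs from about 87% of trials significantly favouring the worse arm with no deaths to about 1% at 60%/10% mortality. The documents give no mortality by failure status from which to choose a row.

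For days on PH treatment, the finding is narrower. The exclusion is ambiguous, it differs between Objectives and Data analysis, and on the allocated-drug reading it measures the arms differently, in a direction that cannot be fixed in advance.

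Both outcomes are secondary. This should be corrected before analysis, but it does not touch the primary analysis or the sample size.

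**What to change.** 1. **Study-drug-free days.** Score surviving treatment failures as zero drug-free days, ranked next to death.
2. **Days on PH treatment.** Replace the study-drug exclusion with one list of PH drugs, identical in both arms: iNO, sildenafil by any route, bosentan and the others to be named. State explicitly whether milrinone and prostin are on it. Make the wording in Objectives and Data analysis agree.

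The cost is outcome wording only. PH-drug use during admission is already an outcome, and the Follow up section collects it after day 14, so no treatment, visit or sample size changes. The downside is that the first outcome becomes a success-weighted measure that overlaps the separately reported failure outcome. Pure time on the allocated drug can still be given descriptively, without a test.
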